#### Additional analysis for percentage point change in ODI

Two additional analyses will be carried out for the primary outcome variable ODI at 6 months. First, an adjusted analysis will be used to control for baseline variables (age, sex, education, smoking status, physical activity, use of pain killers). This multiple linear regression analysis will adjust for potential predictor variables which might reasonably be expected to be predictive of favourable outcomes. We will perform residual analysis to assess model assumptions and goodness-of-fit. Secondly, a subgroup analysis will be performed to detect differences between groups of patients with an ODI normalised score at baseline either less than 40% or equal to or greater than 40% [12].

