The scientific basis to recommend the use of one treatment alternative over another is inadequate or limited and, therefore, more research is needed to study the effectiveness [9–11], and cost-effectiveness [12–15] of treatments for CLBP. According to findings in systematic literature reviews, there is high-quality evidence that spinal manipulation is as effective as other therapies (exercise therapy, standard medical care or physiotherapy) in reducing pain and improving function [10]. Furthermore, there is low-to-moderate evidence for (motor control) exercise to be clinically important, when compared to minimal intervention, and there is moderate-to-good evidence that motor control exercises have similar outcomes as other exercises and manual therapies [11]. There is moderate evidence that multidisciplinary treatments are more likely to have less pain and disability for patients compared to patients receiving usual care or physiotherapy [9]. However, SBU (2015) stated in a comment that the results in Kamper et al. (2015) were uncertain and maybe due to publication bias [9, 16].

In a previous pragmatic randomised controlled trial (RCT) in Sweden, Skargren et al. [12] compared the outcomes and costs of chiropractic care and physiotherapy as a primary treatment for patients with back and neck pain over a 1-year follow-up [14]. No difference in costs and outcomes were demonstrated for the total population. However, subgroup analyses showed that patients with acute, uncomplicated back pain gained more from chiropractic care at a similar cost, whereas patients with chronic back pain gained more from physiotherapy with a slightly reduced cost [12]. Niemisto et al. (2003) found that a combined intervention (advice, physiotherapy, and spinal manipulation) was more effective in reducing pain and disability than a physician consultation alone [13]. There were no significant differences in costs between the treatment groups [13]. In a follow-up study 2 years later, it was indicated that a physician consultation was cost-effective [14]. A cost-effectiveness study conducted alongside a RCT, concluded that spinal manipulation was a cost-effective addition to ‘best care’ for back pain in general practice, but also found that manipulation alone probably was cost-effective compared with manipulation followed by exercise in a UK setting [15].

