### Characteristics of participants

The study includes individuals aged between 18 to 60 years, who are willing to participate in any of the included treatment groups (‘information and advice’; ‘physiotherapy, and information and advice’; ‘chiropractic care, and information and advice’; or ‘chiropractic care, physiotherapy, and information and advice’). All patients give written informed consent. The inclusion and exclusion of study participants is done to mimic the clinical praxis of Swedish primary health care, where the first patient contact usually takes place by phone. Inclusion criteria are: pain located below the costal margin and above the inferior gluteal folds, reoccurring low back pain for at least 3 months, age between 18 to 60 years, can stand or walk independently, and being Swedish speaking and literate. Exclusion criteria are: pain attributable to a known specific pathology (e.g. pain related to tumours, fractures, or fibromyalgia), lack of written informed consent, pregnancy or less than 6 months postpartum or post weaning, been treated for low back pain by a chiropractor and/or physiotherapist in the previous 1 month.

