#### Baseline

Baseline data will be collected during the first visit or at 1–4 days before the first visit at the PCRU. Data on individual characteristics (age, sex, education, smoking status, physical activity, use of pain killers, and pain duration), outcome measures (back pain-related functional limitation, pain intensity, general health, HRQoL, working status) and resource consumption (pharmaceuticals, health care visits, clinical examinations, and hospital days) are collected.

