#### Primary outcome measure

The primary analysis is to evaluate between-group differences in percentage point change in ODI scores at 6 months compared to baseline. One-way analysis of variance (ANOVA) will be used to evaluate the between-group difference for the primary outcome variable ODI at 6 months. A Levine’s test will be employed to check the assumption of equality of variance for the ANOVA. Assumption of normality will be checked by using skewness and normal probability plot. In case of violation of the normality assumption, we will use the non-parametric Kruskal-Wallis H test which does not require the assumption of normality. If the assumption of homogeneity of variance is violated we will use, the Welch or the Brown and Forsythe test. If the overall ANOVA is significant, we will perform further analysis using a Tukey or Games-Howell post hoc pairwise comparison. We will use Games-Howell if there is a violation of the equality of variance assumption. To evaluate effect size, we will present the difference between means, 95% confidence interval and the partial eta-squared (*η*
^2^).

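### Pain duration is collected at baseline but left out, without a stated reason, of the closed covariate list for the additional adjusted ODI regression; the effect is minor and the correction is free

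*Protocol article*

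**What the plan says.** The Baseline subsection of Data collection lists these individual characteristics: "age, sex, education, smoking status, physical activity, use of pain killers, and pain duration". Baseline outcome measures and resource use are listed there separately.

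The section on additional analysis for percentage point change in ODI opens with "Two additional analyses will be carried out for the primary outcome variable ODI at 6 months". The first of the two is a multiple linear regression that will "control for baseline variables (age, sex, education, smoking status, physical activity, use of pain killers". The list stands in brackets, with nothing to mark it as a set of examples. Its purpose is given as being to "adjust for potential predictor variables which might reasonably be expected to be predictive of favourable outcomes". The second is a subgroup analysis split at a baseline ODI of 40%.

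The primary analysis carries no covariates: "One-way analysis of variance (ANOVA) will be used to evaluate the between-group difference for the primary outcome variable ODI at 6 months".

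**The concern.** The regression takes the first six baseline characteristics in the order in which they are collected and stops before the seventh. No reason is given. This looks more like an oversight than a choice, because the stated bar for covariates is low: variables "which might reasonably be expected to be predictive of favourable outcomes". Education and smoking status pass that bar without any supporting evidence in the article. Duration helps to define the condition. Entry requires "reoccurring low back pain for at least 3 months" with no upper limit, so duration can vary widely between participants.

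The adjusted regression is the only analysis of the primary outcome for which the article lists covariates. If the arms happened to differ in pain duration, a reader of a chronic-pain trial might well ask whether that mattered. The regression as listed could not answer, and adding the variable once the data had been seen would be post hoc. If duration does predict change in ODI, some precision is also given up in that analysis.

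**Working it through.** **1. The two lists side by side**

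| Characteristic | Collected at baseline | In the adjusted regression |
|---|---|---|
| Age | yes | yes |
| Sex | yes | yes |
| Education | yes | yes |
| Smoking status | yes | yes |
| Physical activity | yes | yes |
| Use of pain killers | yes | yes |
| Pain duration | yes | **no** |

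Seven are collected and six are used. Pain duration is the only difference. The Statistical analysis section does not name it elsewhere: not in the ANOVA, the subgroup analysis, the mixed models, the GEE or the cost-effectiveness analysis.

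**2. Inputs for the size of the effect**

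- From Required sample size: 150 patients per group, 20% dropout, SD 15, and a difference of 10 ODI points (the MCID).
- Evaluable per group: 150 × 0.8 = 120.
- Partial correlation *r* of pain duration with 6-month ODI change: not given in the article. Assumed range 0 to 0.3.

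The 150 does not follow from the article's own inputs. The standard two-group formula gives 2 × (15/10)² × (1.96 + 0.84)² ≈ 35.3, so 36 evaluable, and 36/0.8 = 45 per group. That is a separate matter. The check below takes 150 only as the number that will be recruited.

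**3. Precision**

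The SE of a pairwise difference without duration is 15 × √(2/120) = 1.936, and the 95% half-width is 1.96 × 1.936 = 3.80. With duration in the model, the SE is 1.936 × √(1 − *r*²). The power column is for a difference of 5.42 points, which 120 per group detects with about 80% power.

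| Assumed *r* | SE | Fall in SE | 95% half-width | Power for 5.42 points |
|---|---|---|---|---|
| 0 | 1.936 | 0% | 3.80 | 79.9% |
| 0.1 | 1.927 | 0.5% | 3.78 | 80.3% |
| 0.2 | 1.897 | 2.0% | 3.72 | 81.5% |
| 0.3 | 1.847 | 4.6% | 3.62 | 83.5% |

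**4. Shift from chance imbalance**

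In standardised units, the difference in mean duration between two arms has an SD of √(2/120). Its 95% limit moves a contrast by 1.96 × *r* × 15 × √(2/120):

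- *r* = 0: 0 points
- *r* = 0.1: 0.38 points
- *r* = 0.2: 0.76 points
- *r* = 0.3: 1.14 points

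**5. Cross-check by a second route**

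Split duration at its median. The 95% limit of imbalance between two arms is 1.96 × √(0.25 × 2/120) = 0.127, or about 13 percentage points. If patients above the median improve by 3 to 8 ODI points less (an assumption), the shift is 0.127 × 3 = 0.38 to 0.127 × 8 ≈ 1.0 points. The two routes give the same order of size.

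**The case against.** The case against is a good one, and most of it limits the point without removing it.

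- *A collection list is not a covariate list.* Baseline variables are often collected only to describe the sample, and the phrase about predictors describes the variables chosen; it does not oblige every qualifying variable to enter. This stands. A reader might infer that the plan breaks its own rule, but the text supports only that duration is a reasonable candidate, left out without explanation.
- *The background does not show that duration is prognostic.* A reader might take the earlier Swedish trial, in which "patients with chronic back pain gained more from physiotherapy with a slightly reduced cost", as evidence that duration predicts outcome. It reports which treatment did better in acute and in chronic pain. That is effect modification, across a contrast that is absent here because every participant has had pain for at least 3 months. This stands.
- *The loss of precision is assumed.* This also stands: at *r* = 0 nothing is gained.
- *Only an additional analysis is touched.* A reader might infer that the main result is exposed to imbalance in chronicity. The primary ANOVA adjusts for nothing, randomisation keeps its comparison unbiased, and its confidence interval already allows for chance imbalance.
- *The full plan may say more.* True of the mixed models, for which the article lists no covariates. It is less persuasive for this regression, because the article does fix the list.
- *Baseline ODI is the bigger gap.* Probably so. It is a separate point, and adding baseline ODI would not in itself adjust for duration.

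**Conclusion.** The omission is confirmed by comparing the two lists. Pain duration is the one individual characteristic that is collected, left out of the adjusted ODI regression without a reason, and named in no analysis in the article.

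The consequence is minor. With 120 evaluable patients per arm, an SD of 15 and an assumed *r* between 0 and 0.3, the SE of a pairwise difference would fall by at most 4.6%. The shift from an imbalance at its 95% limit would be at most about 1.1 points, roughly a tenth of the 10-point MCID. The range for *r* is the reviewer's assumption, and the article offers nothing to narrow it. The size is therefore a bound under that assumption and does not show that precision is in fact lost. Severity is low.

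**What to change.** In the section on additional analysis for percentage point change in ODI, add baseline pain duration to the bracketed covariate list, as a continuous or log-transformed variable, with the form fixed before the data are examined. If the omission was deliberate, one sentence giving the reason would serve instead.

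The cost is one phrase. The variable is already in the baseline questionnaire, so no data collection, sample size or primary analysis changes.

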### Statistical analysis

The main analysis will be conducted as an intention-to-treat (ITT) analysis for all participants that are included in the study [50]. Pattern of missing data and dropout will be examined and if appropriate multiple imputations will be used based on the nature of the missing data. The primary analysis is to evaluate between group differences in change on ODI scores at 6 months. All statistical tests are carried out at the 5% significance level (two-sided).

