#### Secondary outcome measures

Additional analysis of ODI will be done to evaluate the percentage point change in ODI scores and improvement at 3 and 12 months, respectively. Since the trial involves repeated measures data, a linear mixed model will also be used to analyse the secondary outcome measure. To account for repeated measures, to model within-subject variance, and to handle correlated data of continuous variables we will use a linear mixed model. An interaction term will be introduced in the model to examine heterogeneity effect.

The effect of treatment will be evaluated separately for each outcome variable (both primary and secondary) by using a linear mixed model. For binary and ordinal outcome variables a GEE will be employed. The latter model will be used to evaluate the effect of treatment on physical activity at 3, 6, and 12 months.

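### The 40% baseline-ODI subgroup analysis is worded as a comparison of severity groups on change in ODI, and no treatment-by-baseline interaction is tied to it

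*Protocol article*

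**What the plan says.** The article gives two extra analyses of 6-month ODI under the heading "Additional analysis for percentage point change in ODI". One is a regression to "control for baseline variables (age, sex, education, smoking status, physical activity, use of pain killers"; baseline ODI is not in that list. The other is the subgroup analysis: "a subgroup analysis will be performed to detect differences between groups of patients with an ODI normalised score at baseline either less than 40" percent, or at or above it. No test, model or treatment contrast is given for it.

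The primary analysis is defined between arms: "The primary analysis is to evaluate between-group differences in percentage point change in ODI scores at 6 months compared to baseline", by one-way ANOVA and without a covariate.

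Under Secondary outcome measures, a linear mixed model is planned, and "An interaction term will be introduced in the model to examine heterogeneity effect". The variables in that term are not named. The scope of the model is wide: "The effect of treatment will be evaluated separately for each outcome variable (both primary and secondary) by using a linear mixed model". On error rates, the Statistical analysis section says "All statistical tests are carried out at the 5% significance level (two-sided".

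**The concern.** A subgroup analysis should ask whether the difference between arms depends on the subgroup variable. The sentence asks for differences between two sets of patients defined by baseline severity. Because the outcome is change from that same baseline, patients picked for a high starting score will on average fall back, and patients picked for a low one will drift up, whatever treatment they receive.

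The other plausible way to carry it out is a separate arm comparison in each stratum. That avoids the first problem but still does not test effect modification: a significant result in one stratum and not in the other is common when the true effect is the same in both.

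At stake is a statement that a treatment helps severe but not mild patients, or the reverse, that the data do not support. The article says the trial's results should inform guidelines.

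**Working it through.** The plan gives no figure for the subgroup analysis, so there is none to reproduce. From Required sample size I take only SD 15, the 10-point minimal important difference, and 150 per group with 20% dropout, so 150 × 0.8 = 120 evaluable per arm and 4 × 120 = 480 in all. Baseline mean, baseline-to-6-month correlation and the share of patients at or above 40 are not in the article. They are assumptions and are shown as ranges.

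**Reading 1: stratum against stratum on change, no treatment effect.** Take normal scores with SD 15 and the same mean *m* at both times, and correlation *r*. Let z = (40 − m)/15 and p = 1 − Φ(z).

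- Mean baseline above *m* in the upper stratum: 15φ(z)/p.
- Mean baseline below *m* in the lower stratum: 15φ(z)/(1 − p).
- Gap in mean improvement = (1 − r) × the sum of the two.

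For m = 30: z = 0.667, φ = 0.3194, p = 0.2525. The two terms are 18.98 and 6.41, sum 25.39. At r = 0.5 the gap is 0.5 × 25.39 = 12.7 points.

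| m | share ≥ 40 | sum | r = 0.4 | r = 0.5 | r = 0.7 | r = 0.85 |
|---|---|---|---|---|---|---|
| 25 | 16% | 27.19 | 16.3 | 13.6 | 8.2 | 4.1 |
| 30 | 25% | 25.39 | 15.2 | 12.7 | 7.6 | 3.8 |
| 35 | 37% | 24.30 | 14.6 | 12.2 | 7.3 | 3.6 |

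The gap is 3.6 to 16.3 points. With 480 evaluable patients and r from 0.5 to 0.85, the chance of p < 0.05 is 98 to 100%.

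**Reading 2: arms compared separately in each stratum.** Regression to the mean is the same in expectation in every randomised arm within a stratum, so it drops out of the arm difference. What remains is chance.

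- No effect, one test per stratum: P(exactly one significant) = 2 × 0.05 × 0.95 = 9.5%; P(at least one) = 1 − 0.95² = 9.75%. Simulated four-arm ANOVAs give about 9.4 to 9.9% and 9.6 to 10.2%.
- Same true difference Δ in both strata, one pair of arms: SE = 15√(2/n), power = Φ(Δ/SE − 1.96), and P(exactly one significant) = P₁(1 − P₂) + P₂(1 − P₁).

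| Share ≥ 40 | n per arm (low, high) | SE | Δ | power (low, high) | exactly one significant |
|---|---|---|---|---|---|
| 25% | 90, 30 | 2.236, 3.873 | 5 | 0.609, 0.252 | 55% |
| 25% | 90, 30 | same | 6 | 0.765, 0.341 | 59% |
| 25% | 90, 30 | same | 7 | 0.879, 0.439 | 55% |
| 25% | 90, 30 | same | 10 | 0.994, 0.733 | 27% (28% with the t distribution) |
| 50% | 60, 60 | 2.739, 2.739 | 5 | 0.447, 0.447 | 49% |
| 50% | 60, 60 | same | 7 | 0.724, 0.724 | 40% |
| 50% | 60, 60 | same | 10 | 0.955, 0.955 | 9% |

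**Interaction test.** In simulations with four arms of 120 and no treatment effect, the treatment-by-stratum F test (3 df) rejects in 4.4 to 5.0% of trials.

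**The case against.** The strongest reply is that the context settles the meaning. The subgroup analysis is introduced as an analysis of the primary outcome, which is defined between arms, and the research questions concern treatment. A comparison of severe with mild patients that ignores arm answers no question the trial asks. That is fair as to intent, but the sentence as written states the other contrast, and the intended reading still comes with no test of effect modification.

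A reader might infer that regression to the mean would distort the arm comparisons and so create a false treatment effect. It does not: it cancels between randomised arms within a stratum. The 4 to 16 point gap is a difference between severity groups and matters only on the literal reading.

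A reader might also infer that the protocol has no interaction test at all. That goes too far. A term for heterogeneity is planned in a mixed model that also covers the primary outcome. It could be treatment by time, treatment by baseline ODI or something else, so the supportable statement is that none is specified for this subgroup.

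The model could be left to an analysis plan that is not shown, and its absence alone would be no finding. The point here is the contrast that the article does state, which a sound plan would have to replace.

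On size, the high discordance figures belong to effects of 5 to 7 points. At the 10 points the trial is planned for, they fall to 9 to 28%. The two calculations also assume different ranges for the share at or above 40 (16 to 37% implied by the first, 25 to 50% in the second).

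**Conclusion.** The point holds in limited form: the wording fixes a poor contrast, and the one interaction term in the article is undefined and unconnected to it. Neither way of carrying out the analysis as described tests whether the treatment effect depends on baseline ODI.

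The consequence depends on the reading: a near-certain spurious difference between severity groups if it is taken literally, or discordant significance if arms are tested within strata. The first rests on normal scores with equal mean and SD at both times. The second rests on SD 15 for the analysed outcome within strata, 120 evaluable per arm and one pair of arms. This is an additional, non-primary analysis with a single prespecified cut-point, so the primary result is unaffected.

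**What to change.** State that the subgroup question is whether arm differences in 6-month ODI depend on baseline ODI. Test it with an arm-by-baseline-ODI interaction in a model that contains arm and baseline ODI, using either continuous baseline ODI or the prespecified 40% split. Show arm differences with 95% confidence intervals below and at or above 40 as description only. Claim a subgroup effect only on the interaction, and label it exploratory. Name the variables in the mixed-model interaction term and say whether it serves this question.

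The cost is a few sentences and one set of model terms; no new data are needed. The price is low power. For one pair of arms the interaction SE is 15√(2/n_low + 2/n_high), which is 3.87 with half the patients at or above 40 and 4.47 with a quarter. The interaction detectable with 80% power is 2.80 × SE, about 10.9 to 12.5 points, and power for a 10-point difference in effects is about 73% to 61%. A non-significant interaction should therefore not be read as proof of equal effects.

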#### Secondary outcome measures

Additional analysis of ODI will be done to evaluate the percentage point change in ODI scores and improvement at 3 and 12 months, respectively. Since the trial involves repeated measures data, a linear mixed model will also be used to analyse the secondary outcome measure. To account for repeated measures, to model within-subject variance, and to handle correlated data of continuous variables we will use a linear mixed model. An interaction term will be introduced in the model to examine heterogeneity effect.

The effect of treatment will be evaluated separately for each outcome variable (both primary and secondary) by using a linear mixed model. For binary and ordinal outcome variables a GEE will be employed. The latter model will be used to evaluate the effect of treatment on physical activity at 3, 6, and 12 months.

